#### Primary Outcome

The primary outcome is mental health of the participant at 6-months post-inclusion (t3) as measured by the Youth Self Report score (YSR 11-18R; 32). All 112 items will be combined to calculate a total problems score. A t-value above 63 marks the cut-off to a clinically relevant score. Internal consistency of the full scale measured by Cronbach's α is ≥0.93 (32).

#### Secondary Outcomes Participants

Mental health of the participant as measured by the Youth Self Report score (YSR 11-18R; 32). The 112 items can be divided into eight problem subscales (e.g., social problems or aggressive behaviors) and 2 second-level scales (internalizing and externalizing problems). All ten subscale scores will be calculated separately. For the eight problem subscales a t-value above 70 marks the cut-off to a clinically relevant score, while for the internalizing and externalizing problems scales a t value above 63 is considered clinically relevant. Internal consistency ranges for the subscales from α = 0.59–0.84 in a community sample and from α = 0.62–0.90 in a clinical sample (32).

Mental wellbeing of the participants will be measured with the World Health Organization-5 [WHO-5; (35)]. Internal consistency of this very economic scale with a processing time of under 1 min on average, assessed by Cronbach's α is 0.92 (36).

Mental health of the participant as assessed by the German version (37) of the semi-structured clinical interview Kiddie Schedule for Affective Disorders and Schizophrenia Present and Lifetime Version [Kiddie-SADS-PL; (38)] designed to be used by trained interviewers to assess mental disorders according to DSM-IV and ICD-10 diagnostic criteria. For the interview fair to excellent interrater reliabilities for the different scales and for different languages have been reported (39, 40).

Self-efficacy of the participant as measured by the Self-Efficacy Scale [SES; (41)]. This 10 items scale has a good internal consistency, Cronbach's α between 0.8 and 0.9 (41).

Coping strategies of the participant as measured by the Brief Coping Orientation to Problems Experienced Inventory (42). The scale consists of 28 items which form 14 subscales, Cronbach's α for all scales range from 0.50–0.90 (42).

#### Secondary Outcomes Parent(s) and/or Legal Guardian(s)

Proxy mental health of the participant at post-inclusion (t3) as measured by the Children Behaviour Check List (CBCL 6-18R; 32). This tool consists of 112 items, the items of the second part can be divided into eight subscales. All eight subscale scores separately and the full scale score will be calculated. For the eight subscales a t-value above 70 and for the full scale above 63 marks the cut-off to a clinically relevant score. Internal consistency of the full scale measured by Cronbach's α is ≥0.93, while it ranges for the subscales from α = 0.59–0.84 in a community sample and from α = 0.62–0.90 in a clinical sample (32).

#### Covariates

The following variables will be included and assessed for their moderating or mediating role in the evaluation of the iCHIMPS intervention.

##### Covariates Participants

Participant characteristics as measured at baseline by self-report items include age, gender, ethnicity, family composition, previous experiences with mental healthcare providers as well as educational and vocational background.

Working alliance between the participant and the E-Coach will be measured by the Working Alliance Inventory for Guided Internet Interventions [WAI-I, (43)]. This questionnaire is based on the Working Alliance Inventory (44) and was adapted for guided online interventions. The 12 items scale can be divided into 2 subscales and has a Cronbach's α of 0.93 for the whole scale, while the two subscales have α's of 0.93 (task and goal agreement) and 0.89 (bond with therapist).

Social support of the participant as measured by the Oslo Social Support Scale 3 [OSSS-3; (45)]. The internal consistency for this short three item scale is 0.64 as measured by Cronbach's α (46).

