**Methods:**

A two-armed multicentered cluster-randomized controlled trial (cRCT) comparing the clinical- and cost-effectiveness of the iCHIMPS IMI in the intervention group (IG) to a treatment-as-usual (TAU) control group will be conducted. Recruitment will be handled at currently 21 adult mental health clinics throughout Germany. Participating families will be randomly divided into the two groups until the final sample size of 306 participating adolescents (age 12–18) has been reached. The adolescents in the intervention group will receive access to the IMI and can take part in up to eight intervention modules. Assessment will be conducted during the recruitment (baseline), 1-month, 2-months, and 6-month post-inclusion. Primary outcome is the mental health of the participating adolescents at 6-months post-inclusion as measured by the Youth Self Report score. Secondary self-report outcomes are mental wellbeing, self-efficacy, coping strategies and negative effects as well as mental health of the adolescents as reported by their parent(s). Included moderators are sociodemographic characteristics, working alliance, social support and the mental health diagnoses of the parents. Statistical analyses will be conducted on the intention-to-treat principle as well as with additional per-protocol analyses. Additionally, the cost-effectiveness as well as qualitative data concerning the adherence, acceptance, and feasibility of the IMI will be analyzed.

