**Figure 1 F1:**
[figure not shown]
Flow chart.

If the potential family meets the inclusion criteria for families and all necessary parties have signed the informed consent as well as the contact forms, a clinical assessment interview will take place, either at the clinics or via phone. The inclusion and exclusion criteria will be written down and transferred to the study team at Ulm University together with the other forms. This marks the end of the recruitment procedure at the adult mental health clinics.

After the recruitment at the clinics is finalized and the inclusion criteria are fulfilled, the participants and possibly their parents and/or legal guardian(s) will receive a personalized link for the online assessment. After the successful completion of the online baseline assessment (t0) by at least the participant and the parent with the mental disorder, the family is eligible to be included into the trial and will be randomized according to the randomization list by a scientist at Ulm University.

Depending on the group the family was randomized to, an email will contain the explanation of the procedure of the internet-based intervention and the following online assessments (iCHIMPS) or the explanation of why they will not receive access to the internet-based intervention and the procedure of the following online assessments (TAU).

If the participant was assigned to iCHIMPS, he or she is able to log into the internet-based intervention at https://patient.esano-trainings.de and complete the eight consecutive modules of the internet-based intervention at her or his own pace.

All participants (ICHIMPS and TAU) and possibly their parent(s) and/or legal guardian(s) will receive emails with an invitation to the online assessments for t1 (one-month post-inclusion), for t2 (two-months post-inclusion) and for t3 (six-months post-inclusion).

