**Assessment adolescents**					
YSR 11-18R	Mental health	x	x	x	x
WHO-5	Mental wellbeing	x	x	x	x
KIDDI-SADS-PL	Mental health (interview)	x			
SES	Self-efficacy	x	x	x	x
Brief-COPE	Coping strategies	x	x	x	x
SD	Sociodemographic characteristics	x			
WAI-I	Working alliance	x	x	x	x
OSSQ	Social support	x	x	x	x
EQ-5D-Y	Health related life quality	x			x
CAMSHRI-DE	Utilization of the health care system	x			x
QO	Qualitative outcomes				x
NEQ	Negative effects		x	x	x

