**Assessment parent(s) and/or legal guardians**					
CBCL 6-18R	Proxy mental health of the adolescent	x		x	x
M.I.N.I.	Mental health (interview)	x			
OSSQ	Proxy social support of the adolescent	x		x	x
SD	Sociodemographic characteristics	x			

*t0, Baseline; t1, 1 month; t2, 2 months; t3, 6 months; YSR 11-18R, Youth Self Report; WHO-5, World Health Organization-5; KIDDI-SADS-PL, Kiddie Schedule for Affective Disorders and Schizophrenia Present and Lifetime Version; SES, Self-Efficacy Scale, Brief-COPE, Brief Coping Orientation to Problems Experienced Inventory; SD, Sociodemographic characteristics; WAI-I, Working Alliance Inventory for Guided Internet Interventions; OSSQ, Oslo Social Support Scale; EQ-5D-Y, EuroQol-5-Dimensions-Youth; CAMSHRI-DE, Children and Adolescent Mental Health Services Receipt Inventory; QO, Qualitative outcomes; NEQ, Negative Effects Questionnaire; CBCL 6-18R, Children Behaviour Check List; M.I.N.I., Mini-International Neuropsychiatric Interview*.

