#### Moderator and Mediator Analyses

Additional moderator and mediator as well as subgroup analyses will be carried out on an exploratory basis with the above defined covariates.

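### The scale rating alliance with the E-Coach is scheduled before any E-Coach contact, and working alliance is listed as a moderator or mediator although it has no pre-randomisation value and no meaning under TAU

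*Protocol article*

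**What the plan says.** The section Covariates Participants defines the instrument: "Working alliance between the participant and the E-Coach will be measured by the Working Alliance Inventory for Guided Internet Interventions". In Table 2, under the adolescents' assessments, its row reads "WAI-I Working alliance x x x x", and the table legend gives the columns as "t0, Baseline; t1, 1 month; t2, 2 months; t3, 6 months". The row carries no restriction to one arm.

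The Procedure section fixes the order of events. A family becomes eligible and is randomised "After the successful completion of the online baseline assessment (t0) by at least the participant and the parent with the mental disorder". The email to TAU families then contains "the explanation of why they will not receive access to the internet-based intervention". The Intervention section mentions E-Coaches only as human support that can be added to the online programme.

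The analytic role is stated in three places:
- Abstract, Methods: "Included moderators are sociodemographic characteristics, working alliance, social support and the mental health diagnoses of the parents".
- Covariates: "The following variables will be included and assessed for their moderating or mediating role in the evaluation of the iCHIMPS intervention".
- Moderator and Mediator Analyses, on the planned work: "Additional moderator and mediator as well as subgroup analyses will be carried out on an exploratory basis with the above defined covariates".

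**The concern.** There are two separate problems.

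The first is one of timing. A form that asks about the relationship with a coach is scheduled at a visit when nobody has been allocated and nobody has a coach.

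The second is one of role. A moderator of a randomised effect should be a characteristic fixed before randomisation, and at the least must be defined in both arms. A mediator arises after randomisation but must also be defined in both arms, because the first step is to compare it between them. Alliance with an E-Coach meets neither condition. The other moderators named in the Abstract do not share the problem: sociodemographic characteristics, social support and parental diagnoses all have a t0 value that is meaningful in both arms.

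What is at stake is an exploratory objective, the fifth in the article's list. If alliance were analysed under its present label, the result would either not be identified or would depend on answers, or on a code, that carry no information about TAU.

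**Working it through.** **Timing.** Four statements, side by side:
1. The WAI-I rates alliance with the E-Coach (Covariates Participants).
2. It is marked at t0 (Table 2).
3. t0 must be complete before the family is randomised, and access to the programme follows randomisation (Procedure).
4. E-Coaching is described only as part of that programme (Intervention).

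Statements 1, 3 and 4 together leave nothing to rate at t0, so statement 2 conflicts with them. The table can make the distinction: the Negative Effects Questionnaire, which also presupposes treatment, is left blank at t0.

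**Role.** The article gives no figure to reproduce and writes out no model, so the check uses the standard forms of moderation and mediation. Let G = 1 for iCHIMPS and 0 for TAU, let W be the WAI-I score, and take 153 participants per arm (Sample Size and Power Calculations).

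If W exists only in iCHIMPS, every usable row has G = 1. The G column then equals the intercept and G×W equals W.

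| Model | Columns | Rank |
|---|---|---|
| Moderation: 1, G, W, G×W | 4 | 2 |
| Mediation, outcome model: 1, G, W | 3 | 2 |
| Mediation, group-to-alliance path: 1, G | 2 | 1 |
| iCHIMPS only: 1, W | 2 | 2 |

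Filling TAU with a constant c does not help. Then G×W = W − c + c·G, so the moderation model has rank 3 of 4 (checked for c = 0 and c = 1) and the interaction remains unidentified. With c = 0 the mediation outcome model reaches rank 3 of 3. But the group-to-alliance path is then (mean W in iCHIMPS) − c, which moves one for one with an arbitrary code. Only the iCHIMPS-only model is estimable without such a code. It describes an association inside one arm and says nothing about what moderates or mediates the difference between arms.

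**Size.** At the planned 306 participants, 153 per group, with Table 2 applied to everyone and no drop-out:
- Scheduled forms: 306 × 4 = 1,224.
- Forms at t0: 306, and 306 / 1,224 = 25%. Allocation does not yet exist at t0, so these forms cannot be confined to one arm.
- TAU forms at t1 to t3, if given: 153 × 3 = 459.
- Upper bound on unusable forms: 306 + 459 = 765, and 765 / 1,224 = 62.5%.

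The count of 306 holds however the later TAU forms are handled; only the denominator would change.

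**The case against.** The strongest reply is that Table 2 lists instruments by respondent and time, not by arm. The Negative Effects Questionnaire and the qualitative items on adherence and acceptance carry no arm label either. The Procedure section sends assessment invitations to both groups but does not say that every scale goes to both. Routing by arm is a detail that an article may leave to the full protocol. This stands. A reader might infer that TAU adolescents will rate a coach they never had, and so quote 62.5% as the expected waste. The article does not say so, and 62.5% is only an upper bound.

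A second reply is that no interaction or mediation model is written down, model form is normally left to the analysis plan, and a within-iCHIMPS analysis can be estimated. This also stands in part. It would be too strong to say that no analysis of alliance is possible. But the article does assign the variable a moderating or mediating role, and in the usual sense of those words the role cannot be filled. It states no restriction to the iCHIMPS arm.

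Two further inferences lack support. One is that a spurious moderator or mediator result will follow; that needs TAU answers to be both collected and analysed, and neither is stated. The other is that the extra items will add to drop-out; the 50–60% in the sample size section is a general rate for online interventions and is not linked to questionnaire length.

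Finally, all of this work is exploratory. That limits the consequence, but it does not make an unidentified contrast identifiable. None of these replies resolves the t0 entry.

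**Conclusion.** The point holds in two parts. The t0 mark for the WAI-I contradicts the article's own sequence. And working alliance cannot serve as a moderator or mediator of the iCHIMPS-versus-TAU effect, because it has no pre-randomisation value and no meaning in TAU.

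At full enrolment 306 of 1,224 scheduled forms (25%) are unusable, rising to at most 765 (62.5%) if TAU receives the scale after baseline. Both counts ignore drop-out. The remaining 459 forms further assume that every iCHIMPS adolescent has an E-Coach, whereas the article describes human support as optional and varying in amount.

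That TAU has no E-Coach is an inference: TAU has no access to the programme, and coaching is described only within it. No sentence says it outright and none contradicts it.

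The consequence is confined to exploratory analyses. The sample size and the confirmatory YSR contrast at t3 do not depend on alliance.

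**What to change.** 1. Delete the t0 mark for the WAI-I in Table 2 and state that the scale goes to the iCHIMPS group only, at t1, t2 and t3.
2. Remove working alliance from the moderators in the Abstract and from the moderating or mediating variables under Covariates. Describe it as a process variable within the intervention arm.
3. Analyse alliance at t1 as a predictor of YSR change to t3 within iCHIMPS, adjusted for baseline YSR and labelled exploratory and non-randomised. If modules completed are added as a covariate, count only those finished before t1. Later modules may lie on the path from alliance to outcome, and adjusting for them could remove part of the association sought.
4. Recruitment began in May 2021, so leave any t0 WAI-I forms already collected out of the analysis, and likewise any from TAU.

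The cost is one table row and a few words in two sections. Questionnaire length falls, and the sample size and primary analysis stay as they are.

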##### Covariates Parent(s) and/or Legal Guardian(s)

Characteristics of the parent(s) or legal guardian(s) as measured by self-report items including age, gender, ethnicity, family composition, previous experiences with mental healthcare providers as well as educational and vocational background.

Mental health of the mentally ill parent(s) as assessed by the Mini-International Neuropsychiatric Interview [M.I.N.I.; (47)]. This tool was designed to be used by trained interviewers in a face to face setting to assess mental disorders according to DSM-IV and ICD-10 diagnostic criteria. Interrater reliabilities ranging from 0.43 to 0.82 for the different diagnoses have been reported for the interview (48).

Proxy social support of the participant as measured by the Oslo Social Support Scale 3 (OSSS-3; 45). The internal consistency of this short three item scale measured by Cronbach's α is 0.64 (46).

#### Qualitative Outcomes

Open and closed questions concerning the adherence, acceptance, experiences, barriers, facilitators as well as potential drop-outs will be included into the online questionnaire.

#### Economic Outcomes

Health related life quality of the participant assessed by the self-report questionnaire EuroQol-5-Dimensions-Youth [EQ-5D-Y; (49–52)]. The questionnaire consists of two parts. In the first part the participant defines his or her actual health state on the five dimensions mobility, self-care, usual activities, pain/discomfort and anxiety/depression. Each dimension is rated between 1 representing the best health state and 3 representing the worst health state. The overall health state is a 5-digit number representing the rating values for each health state. For the generation of QALYs, the overall health states will be valued using utility value sets generated by means of discrete choice experiments with representative samples from the general population (53, 54). In the absence of a national value set the visual analogue scale provided in the second part of the EQ-5D-Y can be used to value the overall health state.

Utilization of the health care system by the participant as measured by the self-report Children and Adolescent Mental Health Services Receipt Inventory (55, 56). This questionnaire assesses utilization of in- and outpatient health care as well as psychosocial care provided by the child welfare services and school based support provided by the educational system (56).

Health insurance claims data provided by one of the participating German health insurance companies, BARMER, DAK, KKH, TK, MKK, IKK Classic, AOK Baden-Württemberg or AOK Hessen, include information about the utilization of the health care system by members of the participating family who are insured by one of the aforementioned health insurance companies. The claims data consists of all treatment services provided by inpatient and outpatient care, medication, remedies, rehabilitation, and sick leave. All available information can be merged via an pseudonymized identification number for each patient. For every treatment service, all costs from health insurance perspective are documented for the period from January 1^st^ 2018 to June 30^th^ 2022.

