#### Economic Evaluation

The cost-effectiveness analysis follows the net benefit method (63–65). To estimate the incremental cost-effectiveness relation (ICER), the incremental costs for additional healthy life years (QALY) through the internet-based intervention will be determined. Cost information is derived from the CAMSHRI-DE assessment tool and additionally from the resource use documented by the claims data. The stochastic uncertainties of the ICER will be estimated by non-parametric bootstrapping (64, 65). Interpretation of the results will be done on the basis of the cost-effectiveness acceptance curve (64, 65). The claims data analysis will be performed in accordance to the Good Practice of Secondary Data Analysis (GPS) guidelines (66).

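### If no national value set exists, the plan lets the self-rated EQ-5D-Y visual analogue scale stand in for a choice-based utility, and the resulting ratio would not be a cost per QALY

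*Protocol article*

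**What the plan says.** Under Economic Outcomes, the protocol article describes the instrument as "Health related life quality of the participant assessed by the self-report questionnaire EuroQol-5-Dimensions-Youth". Its first part yields a five-digit health state and its second part is a visual analogue scale. QALYs are to be generated as follows: "the overall health states will be valued using utility value sets generated by means of discrete choice experiments with representative samples from the general population". The next sentence opens a second route: "In the absence of a national value set the visual analogue scale provided in the second part of the EQ-5D-Y can be used to value" a given state.

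Under Economic Evaluation, the article makes the QALY the denominator of the cost-effectiveness ratio: "the incremental costs for additional healthy life years (QALY) through the internet-based intervention will be determined". The net benefit method is used, and "Interpretation of the results will be done on the basis of the cost-effectiveness acceptance curve". That section does not mention the visual analogue route. It gives a result obtained that way no separate label and no accompanying sensitivity analysis.

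Table 2 schedules the EQ-5D-Y for adolescents at t0 and t3. Cost-effectiveness against treatment as usual is the third listed aim in the Introduction.

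**The concern.** The two adjacent sentences treat as interchangeable two quantities that are not the same. A value set gives each health state a weight derived from choices made by a general-population sample. The visual analogue scale records how the respondent rates their own health, with no choice or trade-off. That such a rating is not a utility is general health-economic method and is not stated in the article. The article does, however, set a standard for QALY weights itself, and the fallback departs from that standard.

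At stake is how the economic result is read. Net benefit and the acceptability curve both set effects against a willingness to pay per QALY. If the effects are on another scale, the threshold no longer applies to them. A ratio reported as cost per QALY would also not be comparable with ratios based on utilities. The conclusion on the third aim could then depend on which valuation route was taken.

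**Working it through.** The plan states no figure on this point, so there is none to reproduce. The check sets the two sentences side by side and then follows the denominator through the analysis.

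**Step 1: the two routes compared (Economic Outcomes).**

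| Property of the weight | Main route | Fallback |
|---|---|---|
| Source | Representative general-population samples | The participating adolescent, by self-report |
| Method | Discrete choice experiment | Visual analogue rating |
| Role | Values the health state for QALYs | Values the health state in place of the above |

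The fallback concerns the same valuation step as the sentence before it. It is a substitute for the QALY weight and is not offered as an additional outcome.

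**Step 2: where the weight goes (Economic Evaluation).** The ratio is incremental cost divided by incremental QALYs. Net benefit is willingness to pay × incremental QALYs − incremental cost. Both use the weight directly.

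**Step 3: how a change of scale carries through.** The documents give no between-arm difference in utility, rating or cost, so the values here are assumptions chosen only to show the mechanism:
- cost difference of 300 EUR;
- utility difference of 0.04 at 6 months;
- equal baselines;
- area under the curve from t0 and t3.

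QALY gain = 0.5 years × 0.04 / 2 = 0.010. Ratio = 300 / 0.010 = 30,000 EUR.

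Let k be the visual analogue difference (score/100) divided by the utility difference. The gain becomes 0.010 × k and the ratio 30,000 / k:

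| k (assumed) | Gain | Ratio (EUR) |
|---|---|---|
| 0.5 | 0.005 | 60,000 |
| 0.75 | 0.0075 | 40,000 |
| 1 | 0.010 | 30,000 |
| 1.5 | 0.015 | 20,000 |
| 2 | 0.020 | 15,000 |

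The ratio moves with 1/k. In net benefit, willingness to pay × (k × gain) equals (k × willingness to pay) × gain. If k were constant, the acceptability curve would therefore be read at the wrong threshold by the factor k. The documents do not give k. They do not show whether it lies above or below 1, or that the two differences would have the same sign.

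**The case against.** The strongest reply is that the fallback is conditional and optional. The main route is fixed firmly, with sources cited. The article does not say that a national value set is lacking, and the wording only permits the visual analogue scale. This stands: the fallback may never be used, and the point applies only if it is. It does not remove the point, because the rule is written into the plan, leaves the choice open, and carries no separate label for a result obtained that way.

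A second reply is that the article condenses a fuller plan. That is fair for scoring detail. Whether ratings would be used person by person or averaged by state, and whether they would be rescaled so that dead equals 0, may be settled elsewhere, and neither is counted as a gap here. The point does not depend on them. Averaged by state, the weights would still be participants' ratings and not general-population choices.

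Third, only the Youth Self Report contrast at t3 is confirmatory (Clinical Analyses). This limits the weight of the point but does not make a mislabelled denominator correct.

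Three stronger readings are tempting, and the documents do not support them:
- A reader might infer that the fallback would flatter the intervention. Nothing in the plan shows that visual analogue differences would exceed utility differences, and the shift could go either way.
- A reader might take the spread of ratings among adolescents in the same state as the size of the error. The ratio uses differences between arm means, and variation within a state does not by itself bias that contrast.
- A reader might add that adolescents know their arm when they rate themselves. The five dimensions are also self-reported by the same adolescents, so this does not separate the two routes.

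**Conclusion.** The concern holds in a limited, conditional form. If the optional fallback is used, the denominator is not a QALY by the article's own definition, and neither the ratio nor the acceptability curve can be read against a willingness to pay per QALY. The direction and size of the shift cannot be determined from the documents. The tabulated range rests on assumed inputs and shows only that the ratio scales inversely with k.

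The verdict rests on two things: that the scale in the second part of the self-report questionnaire is the adolescent's own rating, as the article describes it, and the general methodological point that such a rating is not a choice-based utility. It does not say that the main valuation route is wrong, that a national value set is missing, or that the clinical results are affected. It is worth correcting before the economic analysis because cost-effectiveness is a stated aim and the correction is cheap.

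**What to change.** Replace the fallback sentence under Economic Outcomes with a rule of this kind: if no German EQ-5D-Y value set is available at analysis, the base-case QALY uses one general-population, choice-based value set from another country, named in advance, and a second such set, also named in advance, is applied as a sensitivity analysis. The visual analogue score is reported as a separate outcome and is not labelled or converted to a QALY.

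This keeps to the standard the article already sets, and naming the sets beforehand removes a choice that could otherwise be made after the data are seen. The cost is one sentence in the plan and one additional run of the economic analysis. No new data are needed, because Table 2 already schedules the EQ-5D-Y, including its five dimensions, at t0 and t3. The downside is that a foreign set may not match German preferences exactly. The second set gives some indication of how much that choice matters.
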